### Follow-up

All participants will participate in a 12-week unsupervised follow-up period immediately after the end of intervention. Telephone follow-up will be performed once every 4 weeks, and records of the medications and rehabilitation therapies will be kept. During the 6- and 12-week follow-up periods (10 weeks and 16 weeks after intervention), participants will be referred for clinical evaluation to assess their functional status, including upper limb function, quality of life, and ADL.

### Outcome assessment

The study period is 16 weeks. Outcomes will be assessed at baseline, after 4 weeks of intervention, at 6-week follow-up, and at 12-week follow-up. All outcomes will be measured by several experienced assessors who are blinded to the randomization group after the baseline visit for evaluation. All assessors will be trained to administer these assessments.

### Primary outcomes

The primary outcomes in this study are the mean change in the scores on both the FMA and WMFT from baseline to 4 weeks intervention and 12 weeks follow-up between the two groups and within groups.

The FMA is widely used for motor function assessment and can reflect the functional level of stroke subjects. Even during the early stage of functional recovery, it can distinguish the level of motor function, particularly for those who have low responsiveness. The upper extremity has a maximum score of 66 points divided into three parts, namely shoulder–arm (36 points), wrist–hand (24 points), and coordination (6 points). The FMA-UE is the most common scale for evaluating upper limb motor function after stroke. It is often used as a gold standard for testing the validity of other scales as well [16, 17]. The FMA-UE has excellent reliability and validity and is sensitive enough for clinical and research practice [18].

The WMFT is the preferred scale for assessing mandatory exercise therapy for improving upper limb functions. It can either assess the quality of the patient’s completion of each activity or determine the time required for the patient to do so. The WMFT has good reliability and validity and high internal consistency [19].

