### Statistical analysis

All allocated subjects will be analyzed using the available data (i.e., on the basis of the intention-to-treat). A multiple imputation method will be used to complete missing data. Continuous variables will be expressed as mean (SD) for normal distribution or median for non-normal distribution, and categorical variables will be expressed as frequencies or percentages. A significance level of 95% (two-sided alpha *P* < 0.05) will be used.

After examining the data for normality (Kolmogorov–Smirnov test), the outcome measures will be analyzed using analysis of variance (assuming normal distribution) or Kruskal–Wallis (non-parametric). Demographic characteristics and other baseline values will be described using descriptive statistics for each group. Intragroup comparisons (changes in the FMA-UE, WMFT, VAS, SIS, and MBI scores before and after treatment) will be performed using the paired *t* test. The statistical significance of the observed differences between the groups will be assessed using 2 × 2 factorial analysis of variance to test the main effect and interaction effects of the two interventions (AT and MT). A statistician blinded to study groups will conduct statistical analysis.

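### The primary outcome spans two scales, two time points and within-group change, with one undivided 0.05 level and no named confirmatory contrast

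*Protocol article*

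**What the plan says.** The Primary outcomes section of the protocol article takes as primary "the mean change in the scores on both the FMA and WMFT from baseline to 4 weeks intervention and 12 weeks follow-up", compared "between the two groups and within groups". The abstract repeats this definition.

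The Statistical analysis section sets one level for the whole trial: "A significance level of 95% (two-sided alpha *P* < 0.05) will be used". Group differences go to a 2 × 2 factorial analysis of variance that tests the AT and MT main effects and their interaction. Within groups, "Intragroup comparisons (changes in the FMA-UE, WMFT, VAS, SIS, and MBI scores before and after treatment) will be performed using the paired *t* test".

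The Sample size section uses FMA-UE only, with an effect size of 0.3, alpha 0.05 and 80% power. It arrives at 112 participants, raised to 136 for attrition (34 per group).

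The aims at the end of the Background are, first, the synergy of AT and MT and, second, whether AT and MT, alone or together, do better than conventional treatment. Under Inclusion criteria, patients are at most 6 months from a first stroke. Under Conventional treatment, every arm may receive physical and occupational therapy without restriction.

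**The concern.** There are three separate faults in what the definition fixes.

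- **Several routes to a positive primary result.** Two scales at two times give four primary change scores. With no rule for combining or ordering them, a significant result on any one can be presented as the primary finding.
- **The contrast is not identified.** The trial has four arms, so a comparison of two unnamed groups does not say which factorial effect is confirmatory.
- **Within-group change has primary status.** In patients within 6 months of stroke who all receive rehabilitation, every arm, control included, can be expected to improve. A before-after gain in an active arm therefore says nothing about synergy or about superiority over conventional treatment.

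At stake is whether a reported positive primary result means what the two aims ask.

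**Working it through.** **Inputs.** Two scales and two time points (Primary outcomes); two-sided 0.05 (Statistical analysis); effect size 0.3, 80% power, 112 evaluable and 136 randomised (Sample size). Evaluable per arm: 112/4 = 28. Randomised per arm: 34. The document gives no correlations between scores and no expected background gain, so these are assumptions and are shown as ranges.

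**1. The plan's own figure.** Read 0.3 as Cohen's f and use noncentral-F power with λ = f²N = 0.09N. Numerator df 2 gives N = 111, or 112 as a multiple of four. Numerator df 1 gives 90 and df 3 gives 126. So 112 is recovered with one measure and the full 0.05. Nothing in it allows for four primary scores.

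**2. Error over four scores, one factorial contrast.** The number of scores is 2 × 2 = 4. If independent:

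1 − 0.95⁴ = 1 − 0.8145 = 0.185.

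By simulation under no effect, for two correlation patterns:

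| Assumed correlation | All pairs equal | Same value between scales and between times, product for cross pairs |
|---|---|---|
| 0.5 | 16% | 16% |
| 0.7 | 13% | 14% |
| 0.8 | 11% | 12% |
| 0.9 | 9% | 10% |

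**3. If both scales had to succeed.** At each time the error is then at most 0.05, so over two times it is at most 2 × 0.05 = 10%. The text states no such rule.

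**4. What adjustment would cost instead.** Bonferroni over four scores gives 0.05/4 = 0.0125 per test. For a one-df factorial effect with f = 0.3, N rises from 90 to 128 evaluable, or 128/0.8 = 160 with 20% attrition. Power at 112 falls from 88% to 74%.

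**5. Within-group paired t test with no treatment effect.** Let the background gain be d SD of the change score. The noncentrality is d√n, which at d = 0.5 is 0.5 × √28 = 2.65 or 0.5 × √34 = 2.92. The chance of p < 0.05 in one arm is:

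| Assumed gain d | n = 28 | n = 34 |
|---|---|---|
| 0.2 | 17.5% | 20.5% |
| 0.3 | 33% | 40% |
| 0.5 | 72% | 81% |
| 0.8 | 98% | over 99% |

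At d = 0.5 and n = 28, at least one of four arms is significant with probability 1 − (1 − 0.723)⁴ = 0.994.

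**The case against.** The strongest case on the other side is that an article condenses the full plan. Alpha allocation and testing order commonly sit in an analysis plan that is not shown, and the Statistical analysis section gives only a general level. It does not say that each test is unadjusted. That stands as a limit: testing each score at 0.05 is an inference from the single stated level. It does not remove the point, because the primary definition itself names four scores and within-group change, and an analysis plan should not have to undo it.

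Independence is also implausible for two arm-function scales measured on the same patients, so 18.5% is an upper illustration. This stands, and the correlated range is the better guide.

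Some stronger readings are tempting, but the document does not support them.

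- A reader might count all three factorial effects on all four scores as one family of twelve tests. The effects answer different questions, the aims rank them, and whether to adjust across them in a factorial trial is disputed. The one-contrast figure is the relevant one.
- A reader might count six endpoints because the WMFT can rate quality "or determine the time required for the patient to do so". That sentence describes the instrument and is not a plan to test both scores.
- A reader might infer that a within-arm gain will be claimed as efficacy. The abstract, aims and Discussion frame every conclusion as synergy or superiority over conventional treatment, and the paired tests are described only as before and after treatment. The fault is the primary status given to within-group change.
- A reader might see two dates for the last visit in "10 weeks and 16 weeks after intervention". The Follow-up and Outcome assessment sections settle it: 4 weeks of intervention plus 12 weeks of follow-up is the 16-week study.

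Sizing a trial on one measure is also no error in itself. It matters here because it shows which endpoint the alpha was spent on.

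**Conclusion.** The point holds in this bounded form. As written, one factorial contrast carries a chance of 18.5% under independence, and about 16% to 9% at assumed correlations of 0.5 to 0.9, of at least one false-positive primary result. That is roughly two to three times the nominal 5% over the correlated range. It rests on taking the general 0.05 as the level of each test and any one score as sufficient. It would be lower if both scales had to succeed.

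The within-group part does not depend on those correlations. The 72% to 81% figure depends on the assumed 0.5 SD gain, but the conclusion does not: a before-after change is confounded with natural recovery and conventional therapy, so it cannot serve either aim at any size of gain.

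**What to change.** 1. Strike within-group change from the primary outcome, in the abstract as well. Report within-arm mean change with a confidence interval, descriptively only.
2. Replace the comparison of two groups with the named 2 × 2 factorial contrasts and say which is confirmatory. The first aim points to the AT × MT interaction, with the main effects second.
3. Name FMA-UE change at week 4, the measure used for the sample size, as the single primary endpoint. Place FMA-UE at 12-week follow-up, then one named WMFT score at a named time, behind it as ordered key secondary endpoints. Another explicit rule, such as an alpha split or a both-must-succeed requirement, would also do if it is written down.

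The cost is protocol and analysis-plan wording and a registry update. With one endpoint and one contrast the 0.05 level used for the sample size stands, so the multiplicity fix does not itself raise N. Whether 0.3 is realistic for the interaction is a separate question. The downside is that WMFT and the follow-up time point lose primary status. Since the Trial status section reports ongoing recruitment, the change must be made blind to outcome data, then dated and documented.

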### Secondary outcomes

The mean change in the scores on the VAS, SIS, and MBI after 4 weeks intervention are considered secondary outcomes.

In this study, the VAS will be used to evaluate the highest overall pain level of the upper limb on the affected side during the week before the assessment. The basic method is to use a 10-cm horizontal line (one marked with 10 scales, with endpoints “0” and “10”), which allows patients to indicate the degree of pain. Zero indicates no pain and 10 indicates the most intense pain. In clinical practice, the VAS is considered the most sensitive and reliable method for measuring pain [20].

SIS is mainly used to evaluate the impact of stroke on the health and quality of life of patients [21]. The scale involves items measuring dysfunction caused by stroke and the impact on the patient’s life, with scores ranging from 0 to 100, and assesses the patients’ overall perceptions of recovery after stroke. The scale includes eight domains (strength, hand function, ADL/instrumental ADL, mobile ability, communication, mood, memory and thinking, and participation) and has a total of 59 items.

MBI is the most commonly used internationally recognized evaluation tool for testing the ability to perform ADL [22]. This scale includes items related to bowel and bladder continence, grooming, toileting, feeding, transfer, walking, dressing, bathing, and going up and down stairs. A normal score is 100, and lower scores indicate greater dependency.

### Safety assessments

Acupuncture may cause discomfort or bruising at the sites of needle insertion, nausea, or feeling faint after each treatment. No adverse reactions caused by MT have been reported to date.

During the course of the study, any accidental injury and sudden illness will be recorded. The degree of symptoms, time of occurrence, duration, and treatment will be documented in the observation table. All adverse events reported should be analyzed regardless of the investigators’ assessments of causality. Serious adverse events will be reported to the ethics committee immediately.

### Data collection and management

The data will be entered into a carefully designed electronic CRF. A dependent research assistant (RA) will be in charge of quality control during the data collection process. The project leader will be responsible for the initial data cleansing, identification, coding, and conversion to the appropriate data analysis format. In addition, an independent data and safety monitoring board will be established to monitor the safety of the trial. It will comprise two professional therapists who are experienced in the rehabilitation of limb movement dysfunction after stroke and who are not directly involved in this study. The data and safety monitoring board is independent and will be responsible for the effectiveness and management of data and reports of adverse events.

Demographic information, medical history and medication, lesions, affected side, handedness, cognitive function, time since stroke, stroke type, rehabilitation history (treatment until the beginning of the study), details of current and upper limb dysfunction treatment received within the previous 3 months, and concomitant medications will be recorded. Data will be obtained through direct questions to patients or a relative or proxy and from medical records. The outcome measure will be performed by an experienced assessor after intervention and follow-up. All forms must be dated and signed by the responsible investigator or one of the authorized staff members.

The project manager will have access to the data, and all data is treated with utmost confidentiality and made anonymous to anyone outside the study. All researchers in this study will receive anonymous copies of all data in order to promote dissemination of study results. The result of our study will be published in a peer-reviewed journal.

### Statistical analysis

All allocated subjects will be analyzed using the available data (i.e., on the basis of the intention-to-treat). A multiple imputation method will be used to complete missing data. Continuous variables will be expressed as mean (SD) for normal distribution or median for non-normal distribution, and categorical variables will be expressed as frequencies or percentages. A significance level of 95% (two-sided alpha *P* < 0.05) will be used.

After examining the data for normality (Kolmogorov–Smirnov test), the outcome measures will be analyzed using analysis of variance (assuming normal distribution) or Kruskal–Wallis (non-parametric). Demographic characteristics and other baseline values will be described using descriptive statistics for each group. Intragroup comparisons (changes in the FMA-UE, WMFT, VAS, SIS, and MBI scores before and after treatment) will be performed using the paired *t* test. The statistical significance of the observed differences between the groups will be assessed using 2 × 2 factorial analysis of variance to test the main effect and interaction effects of the two interventions (AT and MT). A statistician blinded to study groups will conduct statistical analysis.

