Acupuncture originated in ancient China approximately 2500 years ago as an important component of TCM. It has been used for thousands of years in several Asian countries to treat a variety of diseases. Acupuncture is simple and effective and has no adverse drug reactions. It has become a popular topic in the field of rehabilitation medicine in China. However, whether acupuncture promotes recovery from stroke remains controversial. Several studies have demonstrated that acupuncture treatment (AT) may promote the recovery of upper limb dysfunction after stroke [9–11]. One study involving a post-hoc analysis showed that the electrical stimulation group had greater improvements in hand grip (*P* = 0.015) and pinch strength (*P* = 0.007) than the control group after 4 weeks [12]. However, a systematic review showed that the methodologic quality of the included trials was inadequate and that the results may not be reliable because of substantial heterogeneity [13].

Acupuncture is a state-of-the-art TCM treatment widely utilized in China. The advantages of AT are its simplicity, convenience, affordability, and efficacy. The use of AT for the treatment of upper limb dysfunction associated with stroke is in alignment with China’s healthcare development priorities. Furthermore, MT is an important component of modern Western rehabilitation. The combination of AT and MT not only embodies the combination of Chinese and Western medicine but also reflects the integration of modern and traditional rehabilitation. If the rehabilitation program is proven to be effective, then its clinical effectiveness will be important for patients requiring rehabilitation. In addition, it is unknown whether the outcomes of combined AT and MT are superior to those of MT alone because very few studies have compared the two therapies.

Therefore, we designed a 2 × 2 factorial randomized controlled trial to explore the clinical efficacy of AT combined with MT to improve the upper limb motor function of stroke patients. We hypothesized that the synergistic effect of both therapies is greater than the sum of the individual effects of each intervention if they are used separately. AT or MT significantly improved upper limb function outcomes to a similar extent compared with the control group.

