During this trial, our first aim will be to assess the synergistic effects of AT and MT on the recovery of upper limb function after stroke. Our second aim will be to determine whether AT and MT, alone or in combination, are more effective than conventional treatment for the rehabilitation of upper limb dysfunction after stroke.

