### Sample size

Sample size was calculated based on the improvement in FMA-UE scores. Based on similar previous reports, the mean difference and SD were 42.86 ± 3.74 and 41.68 ± 3.44 for AT and conventional therapy, respectively [14]. We expect an effect size of at least 0.3 for outcomes after intervention. A sample size of 112 participants is required to sufficiently detect a target effect size with a type 1 error of 5% (α = 0.05) and 80% power (β = 0.20) by using Gpower 3.1.9.2 software. Considering a 20% attrition rate, a total of 136 participants are necessary, with 34 participants in each group.

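### The plan gives two unreconciled rules for the between-group analysis, and one of them leaves the synergy aim without a prespecified test if normality is rejected

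*Protocol article*

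**What the plan says.** The Background section of the protocol article ranks the aims: "our first aim will be to assess the synergistic effects of AT and MT on the recovery of upper limb function after stroke". The hypothesis makes synergy precise, namely that "the synergistic effect of both therapies is greater than the sum of the individual effects of each intervention". That is a departure from additivity, so it is the AT × MT interaction. The Primary outcomes section defines the primary outcomes as average changes from baseline on the FMA and the WMFT.

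The Statistical analysis section then gives two rules for comparing the groups, in one paragraph:

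- **Rule A, conditional.** "After examining the data for normality (Kolmogorov–Smirnov test", and then "the outcome measures will be analyzed using analysis of variance (assuming normal distribution) or Kruskal–Wallis (non-parametric".
- **Rule B, unconditional.** Group differences will be assessed by "2 × 2 factorial analysis of variance to test the main effect and interaction effects of the two interventions (AT and MT".

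Nothing links A to B. Rule A offers no interaction test on its non-parametric side. It speaks only of the data, so it does not fix whether raw scores, changes or residuals are tested for normality.

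**The concern.** The two rules agree only while normality is accepted. Once the KS test rejects, an analyst who follows Rule A runs Kruskal–Wallis and an analyst who follows Rule B runs the factorial ANOVA. Both could claim to have followed the protocol.

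Under Rule A the consequence falls on the first aim. Synergy is a statement about one contrast of four means, whereas a four-group Kruskal–Wallis test asks whether four distributions are the same. It returns no estimate of synergy, and it does not test the mean change that the protocol makes primary. A pretest on the trial's own data would then change the question being answered, not only the method.

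If both rules are meant to apply, each non-normal outcome has an omnibus rank p-value and a factorial p-value. With no rule for which counts, the choice could be made after both are known.

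**Working it through.** **1. What each rule tests.** Write the four arm means as μ(C), μ(AT), μ(MT) and μ(AT+MT). Synergy in the protocol's sense is

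Δ = μ(AT+MT) − μ(AT) − μ(MT) + μ(C) > 0.

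Rule B tests Δ with 1 df. Four-group Kruskal–Wallis has 4 − 1 = 3 df and responds to any pattern of difference. Two patterns, in SD units and in the order C, AT, MT, AT+MT, show the gap:

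- additive: 0, 0.6, 0.6, 1.2, so Δ = 1.2 − 0.6 − 0.6 + 0 = 0;
- pure interaction: 0.3, −0.3, −0.3, 0.3, so Δ = 0.3 + 0.3 + 0.3 + 0.3 = 1.2.

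A test of synergy should stay at 5% for the first pattern and reject for the second.

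**2. The plan's sample size.** The Sample size section gives 112 evaluable participants, effect size 0.3, α = 0.05 and 80% power. Reading 0.3 as Cohen's f, the noncentrality at N = 112 is f²N = 0.09 × 112 = 10.08. The noncentral F distribution then gives:

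| Numerator df | N for 80% power | Power at N = 112 |
|---|---|---|
| 1 | 90 | 0.882 |
| 2 | 111 (112 as a multiple of 4) | 0.807 |
| 3 | 126 | 0.748 |

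The stated 112 is reproduced with 2 df, although the plan states no df. For what follows, 112 / 4 = 28 per arm, and the benchmark power for the 1-df interaction at f = 0.3 is 0.882.

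**3. Behaviour of the two tests at 28 per arm.** 3,000 simulated trials per cell. Error shapes are assumed and equal across arms. Entries are rejection rates at 5%. Monte Carlo SE near 5% is √(0.05 × 0.95 / 3000) = 0.004.

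| Errors (skewness) | Interaction, all effects zero | Interaction, additive pattern | Interaction, pure interaction | Kruskal–Wallis, additive pattern | Kruskal–Wallis, pure interaction |
|---|---|---|---|---|---|
| Normal (0) | 0.043 | 0.058 | 0.875 | 0.961 | 0.724 |
| Gamma, shape 2 (2/√2 = 1.41) | 0.052 | 0.045 | 0.880 | 0.996 | 0.882 |
| Exponential (2) | 0.042 | 0.043 | 0.878 | 0.997 | 0.956 |
| Lognormal, log-scale SD 0.8 | 0.046 | 0.043 | 0.883 | 1.000 | 0.991 |

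A further set of 1,500 trials per shape gave interaction type I error of 0.046 at skewness 1 (gamma, shape 4) and 0.054 at skewness 2. Over all runs with skewed errors the range was 3.5–6.1%.

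The factorial test therefore keeps its level, and its power stays at the benchmark. Kruskal–Wallis rejects in 96–100% of trials with no synergy and in 72–99% with pure synergy, so its p-value cannot separate the two.

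**4. How often Rule A would switch.** At skewness 1, 28 per arm:

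| What is tested | KS with Lilliefors correction | Uncorrected KS |
|---|---|---|
| Errors alone | 71–73% | 9–10% |
| Pooled scores including 0.6 SD effects | 46–47% | about 3% |

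At skewness 2 the rates are 95–100% with the correction and 45–97% without. The chance of reaching the Kruskal–Wallis branch depends on details that the text does not fix, so no single rate can be quoted.

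**The case against.** The strongest reply is that Rule B carries no normality condition. On a natural reading, Rule A covers the four-group comparison and the factorial ANOVA always tests synergy. An analysis plan that is not shown may say so. This has force: the text does not establish that the synergy aim is lost. It does not clear the protocol, because Rule A is stated for the outcome measures in general and is not subordinated to Rule B. The contradiction is on the page.

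Several stronger readings are tempting and are not supported:

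- *A reader might infer that the first aim becomes untestable whenever scores are skewed.* Rule B contradicts this. The trigger is also the KS result, not skewness itself.
- *A reader might infer that an effective treatment triggers the switch.* With normal errors and additive 0.6 SD effects, the Lilliefors test on pooled data rejected in 3.6% of trials, against 3.8% without effects. With errors of skewness 1, adding effects lowered the rate from 71% to 46%.
- *A reader might infer that Kruskal–Wallis can never test a main effect.* Applied to AT yes/no or MT yes/no, it is a rank-sum test of that factor. The limitation belongs to the four-group form, which the text implies but does not spell out.
- *A reader might infer that the entry limit of FMA-UE ≤ 33 makes floor-limited scores likely.* It is an upper limit at baseline, the primary outcomes are changes, and later scores are not capped. The documents give no distribution of change.
- *A reader might infer that results could not be given in FMA points, or that the switch costs baseline adjustment.* Means or medians remain in scale points, and the stated ANOVA names no baseline adjustment either.

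Any omnibus test, one-way ANOVA included, would also reject under additive effects. That is true, and it is the reason an omnibus test cannot stand in for the interaction.

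**Conclusion.** The concern holds as an internal contradiction with a conditional consequence. The Statistical analysis section states both a pretest switch and an unconditional factorial ANOVA. If the switch governs and KS rejects, the first aim has no prespecified test. If both apply, two p-values compete without a rule.

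The switch is not needed to protect the error rate, since the factorial interaction test stays near 5% under the skewed shapes tried.

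This rests on assumed error shapes with equal spread across arms, complete data, 28 per arm, and 0.3 read as Cohen's f. The 0.6 SD effects are also assumed. The sample size section's own means and SDs give (42.86 − 41.68) / √((3.74² + 3.44²) / 2) = 1.18 / 3.59 = 0.33 SD, so the 96–100% figure would be lower at that size. That Kruskal–Wallis has no interaction term does not depend on any of these assumptions.

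**What to change.** State in the protocol, and in the analysis plan if there is one, that the 2 × 2 factorial linear model is the analysis of every outcome whatever a normality test shows. It should report the AT and MT main effects and the AT × MT interaction as differences in means with 95% confidence intervals.

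Remove the KS/Kruskal–Wallis switch, or demote it to a named sensitivity analysis that tests the same interaction contrast. Either a permutation test or a rank-based factorial test would serve. The permutation test can keep the contrast in scale points. A rank-based test assesses interaction on the rank scale and should be labelled so, because the hypothesis of exceeding the sum of the effects is additive on the score scale.

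The cost is wording only, with no extra participants, visits or data. The change should be made before the outcome data are analysed.

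### The second aim compares AT, MT and AT + MT with conventional treatment, but the analysis section names only factorial main effects and interaction, and the stated 80% power does not apply to those comparisons

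*Protocol article*

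**What the plan says.** The Background (end of section) gives two aims. The first is synergy, with the hypothesis that "the synergistic effect of both therapies is greater than the sum of the individual effects of each intervention". The second is to "determine whether AT and MT, alone or in combination, are more effective than conventional treatment". The Abstract and the Discussion repeat the second aim.

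Statistical analysis assesses differences between groups with "2 × 2 factorial analysis of variance to test the main effect and interaction effects of the two interventions (AT and MT". It also mentions analysis of variance or Kruskal–Wallis for the outcome measures, and paired t tests within groups. It names no contrast of an active arm with the control arm.

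Primary outcomes defines the change in scores "from baseline to 4 weeks intervention and 12 weeks follow-up between the two groups and within groups", although the trial has four arms.

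Sample size cites "42.86 ± 3.74 and 41.68 ± 3.44 for AT and conventional therapy", then states: "We expect an effect size of at least 0.3 for outcomes after intervention". It continues: "A sample size of 112 participants is required to sufficiently detect a target effect size", at α = 0.05 and 80% power. Neither the effect-size metric nor the test is named. With attrition the total becomes 136, or 34 per arm.

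The section on AT combined with MT gives the combined arm 15 minutes of each therapy. The single-therapy arms receive 30 minutes.

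**The concern.** The second aim poses arm-versus-control questions, while the named inference concerns other quantities. The two coincide only if the therapies do not interact, which contradicts the first aim's hypothesis. A significant AT main effect could therefore be taken as evidence that AT given alone beats conventional treatment when the combined arm produced it. No single main effect or interaction term is the combination minus control.

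The power statement adds to the problem. Because the sample-size section cites AT against conventional therapy, a reader may take the 80% to cover that comparison.

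**Working it through.** **1. What the planned terms estimate.** Write C, A, M and AM for the mean changes in the control, AT, MT and combined arms, and I = AM − A − M + C for the interaction.

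- AT main effect = ½[(A − C) + (AM − M)] = (A − C) + I/2.
- MT main effect = (M − C) + I/2.
- AM − C = the sum of the two main effects.

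Each main effect equals the single-therapy contrast only when I = 0. The session times add a further difference: AM − M compares 15 min AT plus 15 min MT with 30 min MT, so it is not AT added to an unchanged amount of MT. An omnibus ANOVA or Kruskal–Wallis test does not show which arm differs from control.

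**2. The protocol's 112.** Inputs: effect size 0.3, α = 0.05, 80% power, four groups. Assumption: 0.3 is Cohen's f. Noncentral F with λ = N × 0.3² and denominator df N − 4; at N = 112, λ = 10.08.

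| Numerator df | Corresponds to | N for 80% | Balanced N | Power at 112 |
|---|---|---|---|---|
| 1 | each main effect, or the interaction | 90 | 92 | 88.2% |
| 2 | no term of a 2 × 2 design | 111 | 112 | 80.7% |
| 3 | four-arm omnibus | 126 | 128 | 74.8% |

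Only 2 numerator df reproduces 112. If 0.3 is a two-group d, a two-sided two-sample t test needs 176 per arm, 352 in two arms.

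**3. Power of one arm against control.** 112/4 = 28 evaluable per arm, error pooled over four arms, df = 108, noncentrality = d × √(28/2).

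- Cited difference: 42.86 − 41.68 = 1.18. Pooled SD = √[(3.74² + 3.44²)/2] = 3.59. d = 0.328. Noncentrality = 0.328 × 3.742 = 1.23, power 23%. With Bonferroni over three contrasts (α = 0.05/3), 12%. With all 34 per arm evaluable, 27% unadjusted.
- Under f = 0.3 the answer depends on the pattern of the four means. For equal additive effects (0, d, d, 2d) the SD of the cell means is d/√2, so d = 0.3 × √2 = 0.42 for each single arm and 0.85 for the combination. Power is about 35% for each single arm and 88% for the combination.

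**4. Size of the misreading.** Assume A = M = C and AM = C + D, in SD units. The AT main effect is D/2 with standard error √(1/28). The interaction is D with standard error √(4/28). Both have noncentrality (D/2) × √28, df 108.

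| D | Noncentrality | AT main effect significant | Main effect significant, interaction not (P × (1 − P)) |
|---|---|---|---|
| 0.6 | 1.59 | 35% | 23% |
| 0.8 | 2.12 | 55% | 25% |
| 1.0 | 2.65 | 75% | 19% |

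The product treats the two orthogonal tests as independent. Allowing for their shared error estimate gives 22%, 24% and 19%.

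**5. Precision.** 95% CI half-width, with t(0.975, 108) = 1.98: arm versus control 1.98 × √(2/28) = 0.53 SD; main effect 1.98 × √(1/28) = 0.37 SD. The ratio is √2, about 1.4.

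**The case against.** The strongest defence is that two main effects and an interaction fully describe four cell means. Every arm-versus-control difference can be obtained from the planned model, and a statistical analysis plan that is not shown may list the contrasts. This stands in part: a reader might infer that the second aim is left untested, and the document does not support that. What it supports is that no named test addresses the aim. An analysis plan could add contrasts, but the published text would still tie between-group inference to other quantities and refer to two groups in a four-arm trial.

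Four other strong readings also fail:

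- That the plan tests main effects alone. It names the interaction, which is the direct test of the first aim.
- That the chance of an unflagged misreading is 35–75%. Those are the rates at which the main effect is significant; they count trials in which the planned interaction test would also be significant. No passage says that main effects will be read as single-therapy effects.
- That f = 0.3 means d = 0.6 and hence about 60% power for each contrast. That conversion holds for two equal groups. Over four arms, f does not fix a pairwise difference, and one contrast can exceed 80%.
- That the named factorial tests are underpowered at the stated effect size. If 0.3 is f for each term, these 1-df tests have 88% power at 112.

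**Conclusion.** The point holds as a mismatch between a stated aim and the stated inference, with a power figure that does not transfer. It should be corrected before analysis, but it does not undermine the factorial design.

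The most secure figure is 23% power for one arm against control at the protocol's own cited difference, at 28 per arm and before any multiplicity control. The statement that 112 matches no term of the design rests on reading 0.3 as Cohen's f, which the protocol does not say. The 19–25% rests on assumed effects in which only the combination works. It illustrates the risk and does not predict this trial's result.

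**What to change.** - **Statistical analysis:** state that the second aim is tested by AT minus control, MT minus control and AT + MT minus control from the same four-cell model. Report each with a 95% CI and with multiplicity control across the three, such as Dunnett or Holm. State that main effects will not be read as the effect of a therapy given alone.
- **Primary outcomes:** replace the reference to two groups with these contrasts.
- **Sample size:** name the effect-size metric, the test and the df behind 112, and restate the power for the planned factorial terms. Add that arm-versus-control power is about 23% at the cited difference and lower after multiplicity control. Do not enter 60% as the figure, because f = 0.3 does not determine it.

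The cost is wording and three contrasts from a model already planned, with no extra patients or visits. The downsides are a less favourable power statement and CIs about 1.4 times as wide as those for a main effect.
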